## 5.6. Dealing with subjects after the study is completed

The principal investigator will provide medical care deemed most appropriate for the subjects, taking the results obtained from this study into account. In addition, although the loan of the JD Mate will cease after the completion of this study, if the research subjects wish to continue IWT, they should consult with the office.

# 6. Case registration methods

## 6.1.　 Case registration

Case registration

1) Registration of cases in this study will be done by contacting the Data Center (in the Center for Clinical Research, Shinshu University Hospital). The principal investigator or research assistant (hereafter referred to as "research staff") will complete the "Registration Form" and submit it to the Data Center with the necessary information regarding research subjects for whom written consent has been obtained and who have been determined to be eligible.

2) The Data Center checks the "Registration Form" for completeness and registers the case in the EDC (UHCT ACReSS).

3) The Data Center will send the "Registration Result Notification Form" to the physician in charge.

4) The principal investigator or research staff will initiate the study after completion of case enrollment.

# 7. Endpoint

## 7.1.　 Primary endpoint

## Percentage change in HbA1c at the beginning of the study and at 20 weeks.

## 7.2.　 Secondary endpoints: Liver fat mass by MRI, abdominal visceral fat and thigh muscle mass by CT, thigh muscle strength by EMG, BMI, VO2 peak (maximal oxygen uptake), insulin sensitivity (blood C-peptide, IRI), HDL cholesterol, LDL cholesterol, triglycerides, systolic blood pressure, mean blood glucose and variability (using FreeStyle Libre Pro), urinary albumin, changes in drug dosage from baseline (start) to 20 weeks (end for some items), frequency of IWT and target achievement rate (at least 60 minutes/week of fast walking).

## 7.3. Safety endpoints：Studies on adverse events (collected only for hypoglycemia and hypotension), serious adverse events (SAEs), and locomotor disorders.

# 8. Observation and examination items

8.1.　 Screening evaluation items

・Patient background：age, gender, medical history (hypertension or not, dyslipidemia or not), smoking history, alcohol consumption history, history of exercise habits, family history of diabetes.

・BMI：height, weight.

・Vital signs: systolic and diastolic blood pressure.

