5.4. Provisions for concomitant medications (concomitant therapy)

## None

## 5.5. Criteria for stopping exercise therapy

1 Severe complications (motility disorders, hypoglycemia, hypotension) occur.

2 If an attending physician judges that continuation of the exercise therapy is difficult.

3 Criteria for discontinuation of study treatment

（1）When the individual subject of the research withdraws his/her consent.

（2）If it becomes impossible to continue the study treatment due to the occurrence of adverse events, etc.

（3）If found to be ineligible case.

（4）If the subject does not come to the hospital due to relocation, etc.

（5）If the study physician determines that the study should be discontinued.

（6）If the study is discontinued.

※ Temporary interruption of study is not considered a discontinuation, and study will be resumed as soon as it can be resumed.

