8.4.　 Post-End Assessment Items

・Surveys for adverse events (collected only for hypoglycemia and hypotension), serious adverse events (SAEs), and locomotor disorders.

Observation, Inspection and Reporting Schedule

|  | **screening** | **previous observation** | **Start Date** | **4 w** | **8w** | **12w** | **16w** | **18w** | **20w** | **after the end** | **time of cessation** |
| --- | --- | --- | --- | --- | --- | --- | --- | --- | --- | --- | --- |
|  |  |  | **baseline** | **±2w** | **±2w** | **±2w** | **-2w　+1ｗ** | **±1w** | **±2w** | **The items implemented from 20 weeks to 28 weeks of the start date.** |  |
| Patient Background | ○ |  |  |  |  |  |  |  |  |  |  |
| Body Composition Assessment |  | ○ |  |  |  |  |  |  |  | ○ |  |
| Physical fitness test |  | ○ |  |  |  |  |  |  |  | ○ |  |
| Interval fast walking |  |  |  |  |  | （20ｗ+ Until the end） |  |  |  |  |  |
| Dietary survey | ○ |  |  |  |  |  |  | ○ |  |  |  |
| Calorie consumption | ○(1w) |  |  |  |  |  |  | ○(1w) |  |  |  |
| BMI | ○ |  | ○ |  | ○ | ○ | ○ |  | ○ |  | (Weight only) |
| Insulin sensitivity |  |  | ○ |  |  |  |  |  | ○ |  |  |
| Blood test | ○ |  | ○ | ○ | ○ | ○ | ○ |  | ○ |  |  |
| Urinalysis | ○ |  | ○ |  |  |  |  |  | ○ |  |  |
| Blood pressure | ○ |  | ○ | ○ | ○ | ○ | ○ |  | ○ |  | ○ |
| Blood glucose level variation | ○(2w) |  |  |  |  |  |  | ○  (18~20w) | |  |  |
| concomitant medications |  |  | ○ |  |  |  |  |  | ○ |  | ○ |
| Survey on locomoter disorders |  |  | ○ | ○ | ○ | ○ | ○ | ○ | ○ | ○ | ○ |
| Adverse events |  |  |  |  |  |  |  |  |  | ○ | ○ |

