# 9. Management of adverse events

## 9.1.　 Definition of adverse events

### 9.1.1.　 Definition of adverse events

The term "Adverse Event" shall mean any unwanted or unintended injury or illness or its symptoms (including abnormal laboratory values) that occurs to a research subject, whether or not causally related to the research being conducted.

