### 11.2.4.　 Analysis on safety endpoints (analysis population: SAS)

We will prepare and evaluate a list of investigations regarding adverse events (hypoglycemia and hypotension will be collected), serious adverse events (SAEs), and locomotor disorders. In addition, frequency counts are also performed as necessary.

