# 12. Completion and submission of case report forms

## 12.1.　 Forms and submission deadlines

Case report forms will be submitted by EDC (Electronic Data Capture System). The principal investigator, research assistant, and collaborator in charge will submit data using EDC as the study progresses. If the form is to be completed by someone other than the physician in charge, confirmation from the physician in charge will be obtained.

Reportable submission period

| No. | Type | Reporting Period |
| --- | --- | --- |
| 1 | Registration form | After obtaining consent |
| 2 | Case Report_Patient Background | Within 2 weeks of each scheduled visit |
| 3 | Case Report_Clinical Laboratory Data | Within 2 weeks of each scheduled visit |
| 4 | Case Report_Body Composition Assessment by Imaging Studies | Within 2 weeks of each scheduled visit |
| 5 | Case report_VO2 peak and isometric leg muscle strength measurements | Within 2 weeks of each scheduled visit |
| 6 | Case Report_Training | Within 2 weeks of each scheduled visit |
| 7 | Case Report_Daily Calorie Consumption | Within 2 weeks of each scheduled visit |
| 8 | Case Report_Concomitant medications | Within 2 weeks of each scheduled visit |
| 9 | Case Report_Adverse Events | Within 2 weeks of each scheduled visit |
| 10 | Musculoskeletal Disorders Questionnaire | Within 2 weeks of each scheduled visit |
| 11 | Case report_discontinued | Within 2 weeks of treatment discontinuation or dropout |

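### A non-serious adverse event that ends interval walking training enters no safety endpoint or listing unless it is hypoglycaemia, hypotension or a locomotor disorder

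*Protocol*

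**What the plan says.** Section 9.1.1 of the protocol defines an adverse event broadly, as "any unwanted or unintended injury or illness or its symptoms (including abnormal laboratory values) that occurs to a research subject", whether or not it is related to the research.

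Section 5.5 gives several routes by which exercise or study treatment ends:
- Item 1 names specific complications: "Severe complications (motility disorders, hypoglycemia, hypotension) occur".
- Item 2 is a matter of judgement: "If an attending physician judges that continuation of the exercise therapy is difficult".
- Item 3(2) covers adverse events in general: "If it becomes impossible to continue the study treatment due to the occurrence of adverse events, etc".

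The safety data are narrower. Section 7.3 lists "Studies on adverse events (collected only for hypoglycemia and hypotension), serious adverse events (SAEs), and locomotor disorders". Section 8.4 repeats the limit for the assessment itself: "Surveys for adverse events (collected only for hypoglycemia and hypotension), serious adverse events (SAEs), and locomotor disorders". Section 11.2 restates it, with musculoskeletal in place of locomotor. Section 11.2.4 builds the analysis from the same categories: "We will prepare and evaluate a list of investigations regarding adverse events (hypoglycemia and hypotension will be collected), serious adverse events (SAEs), and locomotor disorders", with frequency counts where needed.

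Section 9.2 has adverse events noted in the medical record. The table in section 12.1 includes, as form 11, "Case report_discontinued", due within two weeks of discontinuation or dropout. The schedule in section 8.4 marks adverse events in the column for cessation.

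**The concern.** The rule for stopping treatment and the rule for collecting safety data differ in scope. Item 3(2) of section 5.5 has no list of event types. The collection rule has one, and it makes no exception for events that end treatment.

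An adverse event that makes a participant give up the intervention bears directly on tolerability. The trial has a single arm and no control, so its safety account rests on what is listed for these participants. If the plan is followed exactly, the listing can be empty for someone who stopped because of an adverse event.

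**Working it through.** The protocol states no power or error rate that bears on this point. The target of 70 is set on feasibility (section 11.1), so there is no figure to reproduce. The check is a comparison of sections.

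**Which treatment-ending events reach the safety result?**

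| Event that ends IWT | Collected under 7.3, 8.4 and 11.2? | In the 11.2.4 listing? |
| --- | --- | --- |
| Hypoglycaemia or hypotension | Yes | Yes |
| Locomotor disorder | Yes | Yes |
| Any event meeting a criterion in 9.1.2 (serious) | Yes | Yes |
| Non-serious event of any other type | No | No |

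The gap is the last row only. Such an event meets the definition in 9.1.1 and can end treatment under 5.5 item 3(2). It is noted in the medical record (9.2), and the stop is reported on form 11 (12.1). No section says that form 11 records the event, or that its content feeds the safety analysis.

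**Is the last row realistic?** Section 9.4 cites an exercise study in 251 patients with type 2 diabetes: hypoglycaemia 3%, trauma 8%, locomotor disorders 17%. Trauma is counted apart from locomotor disorders and is not a collected category here.

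- Expected participants with trauma at that rate: 70 × 0.08 = 5.6.
- Probability of at least one: 1 − (1 − 0.08)^70 = 0.997.

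These figures describe occurrence of trauma. They do not estimate missed stops: some trauma would be captured as serious or locomotor events, and not all of it would end IWT.

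**Size.** One unlisted stop is 1/70 = 1.4% of the target enrolment. The protocol gives no rate p of stopping for non-serious events of other types. Purely as an assumed range, with expected count 70p and probability of at least one 1 − (1 − p)^70:

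| Assumed p | Expected count | Probability of at least one |
| --- | --- | --- |
| 1% | 0.7 | 0.51 |
| 2% | 1.4 | 0.76 |
| 5% | 3.5 | 0.97 |

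Nothing in the protocol anchors this range, the true rate could be zero, and the conclusion does not depend on it.

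**The case against.** The strongest defence is that the restriction is deliberate and consistent. The same scope appears in the summary and in sections 7.3, 8.4, 11.2 and 11.2.4. It matches the risks that section 9.4 expects and the complications named in 5.5 item 1, and serious events of any type are added. Targeted collection is a legitimate choice in an exploratory study that section 14 regards as less invasive, and a broad definition combined with targeted collection is not a contradiction. All of this stands as a defence of limiting routine collection. It does not explain why events that end treatment fall under the same limit when 5.5 item 3(2) reaches beyond the named types.

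A second defence is that form 11 may record the reason, and that a table of discontinuations by reason is commonly left to the statistical analysis plan. The first half stands in part: the form's fields are not shown, and the reason may be recoverable. The second half does not remove the point, because the limit is written into the protocol's endpoint definition and collection rule. Section 11 leaves only technical analysis details to the analysis plan.

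Three stronger readings might be inferred, and the documents do not support them:
- *That these events leave no trace.* The medical record holds the event, and form 11 reports the stop. The omission is from the safety endpoints and listing.
- *That the conclusion on usefulness is biased.* Section 1 defines usefulness by glycaemic control and body composition, and the efficacy analyses are untouched. A stop may also show in the IWT frequency and target-achievement endpoint (7.2), though without its cause.
- *That events causing a temporary interruption are lost in the same way and need the same repair.* Section 5.5 says an interruption is not a discontinuation, so form 11 would not be triggered. Capturing interruptions would need ongoing collection, and no harm from their absence has been shown.

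**Conclusion.** The point holds in a limited form. As written, a non-serious adverse event outside hypoglycaemia, hypotension and locomotor disorders can end IWT under section 5.5 item 3(2) without entering any safety endpoint or listing. The safety result would then omit a treatment-ending event and look somewhat better than the experience of the participants.

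The number affected cannot be derived from the protocol and may be zero. Each case would be 1.4% of 70. The conclusion rests on reading 5.5 item 3(2) as it is written, without a list of event types, and on no section bringing the content of form 11 into the safety analysis. The correction is worth making because it is cheap and the assessment at which to do it is already scheduled.

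**What to change.** - In sections 7.3, 8.4, 11.2 and 11.2.4, add one sentence exempting from the restriction any adverse event that leads to discontinuation of IWT, whatever its type or seriousness.
- At the cessation assessment already in the schedule, record the event term and date, using the adverse event form (form 9) and the discontinuation form (form 11).
- In section 11.2.4, list and count these events in the safety analysis set.

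The cost is one sentence per section and one form field, with no added visit or procedure. The safety profile may look slightly less favourable. Routine collection of other non-serious events stays restricted, and the efficacy analyses and clinical stopping rules do not change.

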8.2.　 Beginning and End Endpoints

・Body composition evaluation: liver fat content by abdominal MRI, abdominal visceral fat content by CT, thigh muscle mass by CT.

・Thigh muscle strength using isometric lower limb muscle testing equipment.

・Physical fitness measurement (using of JD Mate): VO2 peak (maximum oxygen uptake), target level value for training, maximum heart rate.

・Mean blood glucose and blood glucose variability（using of FreeStyle Libre Pro）

・Daily calorie consumption (using of JD Mate): calorie consumption, number of steps, measurement time (minutes)

・Dietary survey

・Concomitant medications: changes from start to end of diabetes medications (insulin, oral medications), hypertension medications, and lipid disorder medications.

・Insulin sensitivity*: blood CPR, IRI

・Blood tests*: HDL-C, LDL-C, triglycerides, BUN, Cre, eGFR, AST, ALT, fasting blood glucose, HbA1c.

・Urinalysis*: Urinary albumin (creatinine equivalent)

・Vital signs*: systolic and diastolic blood pressure.

・Body weight *

　*…Also evaluate at 4, 8, 12, 16, and 18 week visits.

8.3.　 Evaluation items during the study period

・Training (using of JD Mate): calories burned during IWT, number of steps, training time (minutes).

8.4.　 Post-End Assessment Items

・Surveys for adverse events (collected only for hypoglycemia and hypotension), serious adverse events (SAEs), and locomotor disorders.

Observation, Inspection and Reporting Schedule

|  | **screening** | **previous observation** | **Start Date** | **4 w** | **8w** | **12w** | **16w** | **18w** | **20w** | **after the end** | **time of cessation** |
| --- | --- | --- | --- | --- | --- | --- | --- | --- | --- | --- | --- |
|  |  |  | **baseline** | **±2w** | **±2w** | **±2w** | **-2w　+1ｗ** | **±1w** | **±2w** | **The items implemented from 20 weeks to 28 weeks of the start date.** |  |
| Patient Background | ○ |  |  |  |  |  |  |  |  |  |  |
| Body Composition Assessment |  | ○ |  |  |  |  |  |  |  | ○ |  |
| Physical fitness test |  | ○ |  |  |  |  |  |  |  | ○ |  |
| Interval fast walking |  |  |  |  |  | （20ｗ+ Until the end） |  |  |  |  |  |
| Dietary survey | ○ |  |  |  |  |  |  | ○ |  |  |  |
| Calorie consumption | ○(1w) |  |  |  |  |  |  | ○(1w) |  |  |  |
| BMI | ○ |  | ○ |  | ○ | ○ | ○ |  | ○ |  | (Weight only) |
| Insulin sensitivity |  |  | ○ |  |  |  |  |  | ○ |  |  |
| Blood test | ○ |  | ○ | ○ | ○ | ○ | ○ |  | ○ |  |  |
| Urinalysis | ○ |  | ○ |  |  |  |  |  | ○ |  |  |
| Blood pressure | ○ |  | ○ | ○ | ○ | ○ | ○ |  | ○ |  | ○ |
| Blood glucose level variation | ○(2w) |  |  |  |  |  |  | ○  (18~20w) | |  |  |
| concomitant medications |  |  | ○ |  |  |  |  |  | ○ |  | ○ |
| Survey on locomoter disorders |  |  | ○ | ○ | ○ | ○ | ○ | ○ | ○ | ○ | ○ |
| Adverse events |  |  |  |  |  |  |  |  |  | ○ | ○ |

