## 9.4.　 Predicted adverse events

The risk of developing exercise-induced locomotor disease, hypoglycemia, and hypotension is expected.

Adverse events reported for resistance exercise and aerobic exercise in 251 patients wity type 2 diabetes between 39 and 70 years of age, are as follows.

Hypoglycemia frequency 3% (no severe hypoglycemia), trauma frequency 8%, locomotor disorders (upper and lower extremity joint pain, back pain) frequency 17%^5)^.

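### Hypoglycaemia and hypotension, two named safety endpoints, have one scheduled query per participant with a 20-28 week look-back, although suitable visits already exist; non-serious trauma has no explicit collection category

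*Protocol*

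**What the plan says.** **Timing.** Section 8.4, headed as post-end assessments, lists "Surveys for adverse events (collected only for hypoglycemia and hypotension), serious adverse events (SAEs), and locomotor disorders". In the schedule that follows, the adverse event row has two marks: the post-end column, described as "The items implemented from 20 weeks to 28 weeks of the start date", and the cessation column. It is blank at the start date and at weeks 4, 8, 12, 16, 18 and 20. The row directly above, "Survey on locomoter disorders", is marked at the start date, at all six of those visits, after the end and at cessation. Section 8.3, on items evaluated during the study, lists only training data.

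**Forms.** Section 12.1 includes "Case Report_Adverse Events" among the forms due within two weeks of every scheduled visit.

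**Scope.** Section 9.1.1 defines an adverse event as "any unwanted or unintended injury or illness or its symptoms (including abnormal laboratory values) that occurs to a research subject". Sections 7.3, 8.4, 11.2 and 11.2.4 restrict collection to hypoglycaemia and hypotension, together with serious adverse events and locomotor disorders. Section 9.4 names locomotor disease, hypoglycaemia and hypotension as the expected risks. It then cites rates from 251 patients in an earlier trial of resistance and aerobic exercise: "Hypoglycemia frequency 3% (no severe hypoglycemia), trauma frequency 8" (the last figure is also a percentage), and locomotor disorders at 17%.

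**The concern.** Hypoglycaemia and hypotension are named safety endpoints of a 20-week exercise programme. Both are usually brief and may leave no trace by the time someone asks. Followed as written, the schedule provides one question, put 20 to 28 weeks after the start, to people who have already attended six times since then. Events not remembered or not noted at the time cannot be recovered at analysis.

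Expected counts are small, so one or two lost events change what the trial would report on safety. The restricted scope adds a lesser problem: an injury during fast walking meets the protocol's definition of an adverse event, but unless it is serious or counts as a locomotor disorder, no term provides for it.

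**Working it through.** The protocol states no figure that could be reproduced here; the sample size of 70 rests on feasibility (section 11.1). The check is a reading of the schedule, followed by illustrative arithmetic.

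**1. Scheduled queries per participant**

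| Item | Start | 4w | 8w | 12w | 16w | 18w | 20w | After end (20-28w) | Cessation |
|---|---|---|---|---|---|---|---|---|---|
| Locomotor survey | yes | yes | yes | yes | yes | yes | yes | yes | yes |
| Adverse events | no | no | no | no | no | no | no | yes | yes |

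A completer has one adverse event query, with a look-back of 20 to 28 weeks. Nominal gaps between visits are 4 weeks up to week 16 and 2 weeks after that. The look-back is therefore 20/4 = 5 to 28/4 = 7 times the longest nominal gap. The locomotor row shows that the table marks repeated collection where it is intended, so the two marks in the adverse event row are hard to read as shorthand for an end-of-study summary.

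**2. Does section 12.1 close the gap?** There are two readings.
- It means reporting after each visit. It then conflicts with the schedule, which asks for nothing at those visits.
- It is a generic deadline. The same wording is attached to the patient background form, and patient background is marked only at screening. It then adds no data collection.

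Under either reading the documents need a change.

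**3. Do other data close the gap?**
- Continuous glucose monitoring covers two weeks before the start and weeks 18 to 20 (section 5.3 and schedule), so 20 - 2 = 18 of the 20 training weeks are not covered. It gives no information on hypotension.
- Blood pressure and blood tests are marked at weeks 4, 8, 12, 16 and 20. They are measurements at the visit and do not show transient events between visits.
- Section 9.2 requires a note in the medical record when an adverse event is observed. It does not require anyone to ask.
- Serious adverse events are reported promptly when recognised (section 9.3), and locomotor disorders are surveyed at every visit from the start date. These two categories are captured during the study.

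**4. Scale.** Assumption: the rates cited in section 9.4 carry over to these 70 participants.
- Hypoglycaemia, p = 0.03: expected 70 × 0.03 = 2.1; P(at least one) = 1 - 0.97^70 = 0.881.
- Trauma, p = 0.08: expected 70 × 0.08 = 5.6; P(at least one) = 1 - 0.92^70 = 0.997.
- Two hypoglycaemia cases found: 2/70 = 2.9%, exact 95% CI 0.3% to 9.9%.
- Both lost: 0/70, two-sided 95% upper limit 1 - 0.025^(1/70) = 5.1%.

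The documents give no rate for hypotension and none for how often events are forgotten. Losing both cases is therefore an illustration of sensitivity, not a forecast.

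**The case against.** The case for leaving the plan alone has several parts.

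- **Section 8.4 does not by itself fix timing.** It names the locomotor survey in the same sentence, yet the schedule marks that survey at every visit. This stands. The finding rests on the schedule row, and section 8.4 needs tidying for both items.
- **Section 12.1 may already provide reporting after each visit.** If so, there is no long look-back. This is possible, but the schedule would then be wrong, and a site following the schedule would still ask only once. For the same reason, a reader who infers a flat contradiction goes too far: the wording may be a generic deadline.
- **Safety information does arise during training.** This stands. A reader might infer that investigators would see no structured safety data during the exercise period, or that all adverse events are assessed only once. The documents do not support either inference: locomotor surveys, blood pressure, blood tests and serious adverse event reporting all run during the 20 weeks. Other non-serious events are outside the stated scope, not collected once.
- **Under-reporting is not demonstrated.** This stands as to wording. Notes made under section 9.2 could feed the post-end entry. The supportable claim is a risk of under-ascertainment, not a rate known to be falsely low.
- **The protocol does not predict 8% trauma for this study.** This stands. The figure is cited from an earlier trial of a different exercise programme in patients aged 39 to 70, and the protocol's own sentence on expected risks does not name trauma. Nor can one say that trauma is recorded nowhere: observed events go into the medical record, and the locomotor questionnaire, whose content is not shown, may pick some up.
- **The restricted scope is a deliberate choice, consistently stated.** This stands as to consistency. The protocol still does not square that choice with its own broad definition.
- **The effect is modest.** The two intervals in the illustration overlap widely, no safety hypothesis depends on them, and the study is exploratory with an unaffected HbA1c endpoint. This bears on severity but does not remove the gap.

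**Conclusion.** The point holds for hypoglycaemia and hypotension. The schedule gives each participant one query, after the end or at cessation; for completers the look-back is 20 to 28 weeks, although visits that could carry the question already take place. Section 12.1 does not rescue this under either reading, and the other data collected do not cover transient events between visits.

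The consequence is a risk of under-ascertainment of unknown size. If the cited 3% applied, only about two hypoglycaemia cases would be expected, so the reported result would be sensitive to each one. The secondary point also holds, in limited form: non-serious trauma meets the section 9.1.1 definition but has no explicit collection category, and about 5.6 of 70 participants would be affected if the cited 8% applied.

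This should be fixed. It does not threaten the primary endpoint, and serious adverse events and locomotor disorders are captured as the study runs.

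**What to change.** 1. Mark the adverse event row at weeks 4, 8, 12, 16, 18 and 20, and keep the existing marks after the end and at cessation.
2. Align section 8.4 with the schedule, for the locomotor survey as well, and state in section 12.1 that the adverse event form is completed at each of these visits.
3. Add exercise-related trauma and falls to the terms collected at the same visits, in sections 7.3, 8.4, 11.2 and 11.2.4. Alternatively, keep the restricted scope and reconcile it explicitly with the definition in section 9.1.1.

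The cost is an amendment to the schedule and the case report form, and a few minutes at visits that already take place. No extra attendance is needed. How the events are summarised can be left to the statistical analysis plan.
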